### Staffing

For the purposes of this study, the following staffing will be recruited: a project manager, who will facilitate GP engagement, patient recruitment and consent, data collection, data management and reporting; a community-embedded specialist in geriatric medicine to provide comprehensive geriatric assessments and management plans at the GPs’ rooms; and two community-based care coordinators (enablement officers), who will facilitate access to healthcare services, social supports and self-management options. These positions are solely community embedded, designed to coordinate hospital-based specialist geriatric and other primary care services, such as social care services, allied health and rehabilitation services.

### Participants’ eligibility criteria

#### Sample size

Bird et al. [5] reported suitable comparative outcomes from a similar study. Following the stepped wedge study design with repeated cross-sectional samples recommendations of Barker et al. [16] and the applied parameters of Bird et al. [5], at least two clusters will be randomised at each step to ensure the nominal 5% significance level. Bird et al. [5] reached statistical significance using ANOVAs and *t* tests over three measures: ED presentations, hospital admissions and bed days. Pre verses post improvement for these three measures was 10%, 25% and 18% respectively. Following consultations with clinical and statistical experts, a conservative effect size across ED and in-patient services utilisation of 9%, a 10% intra-cluster correlation and between-cluster variations of 30% were assumed for the current study. The intervention will be staged in steps, each with at least two clusters/GPs, totalling a minimum of 10 GPs (clusters), who will each recruit 10–12 participants to the study. Allowing for 25% censoring, a sample size of 120 participants will be required, which will provide 80% power to detect a 9% difference (effect size) in service utilisation with statistical significance at the 5% level. The study design incorporates the effects of ‘time’. Sample size calculations were performed using the stepped wedge command in STATA 15 [18].

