**Methods/design:**

This multicentre randomised controlled trial uses a stepped wedge cluster design with repeated cross-sectional samples. General practitioners (GPs; *n* ≥ 10) will be randomised as ‘clusters’ at baseline using simple randomisation. Each GP cluster will recruit 10–12 participants. Data will be collected on each participant at 3-month intervals (− 3, 0, 3, 6 and 9 months). The primary outcome is health and social service utilisation as measured by Emergency Department presentations, hospital admissions, in-patient bed days, allied health and community support services. Secondary outcomes include functional status, quality of life and participants’ satisfaction. Cost-effectiveness of the intervention will be assessed as the change to cost outcomes, including the cost of implementing the intervention and subsequent use of services, and the change to health benefits represented by quality adjusted life years.

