Published programmes utilising the GEM in Australia have shown promising results, including the Victorian Hospital Admission Risk Program, which reported 35% fewer Emergency Department (ED) attendances, 52% fewer admissions and 41% fewer days in hospital [5]. Similarly, the Reengineered Hospital Discharge Program [6], Better Outcomes for Older Adults Through Safe Transitions and State Action on Avoidable Re-hospitalisations programmes have shown improvements in reducing hospital readmissions and hospital utilisation such as length of stay [7]. The Geri-FITT model of care which involves a ‘floating interdisciplinary geriatric team’ to provide continuity of care through developing and facilitating transitional care plans and educating patients and care providers about geriatric care principles has demonstrated improved quality care transitions and greater patient satisfaction [8].The most similar study to the one proposed here was the ‘Patients First Model of Care’, which targeted people over 55 years old who frequently presented to the ED or were at risk of presenting to the ED. This study involved a comprehensive needs assessment by a community-based care facilitator, with care coordination and facilitation of access to a suite of services including allied health therapies where required. Findings from this community coordinated study reported a 27.9% reduction in hospital admissions and a 19.2% reduction in bed days without increasing overall costs to the health system [9].

Recent research on care transitions of older people across acute, sub-acute and primary care identified underutilisation of the GEM model in a community setting in north-eastern Australia [4]. In this region, an integrated model of comprehensive geriatric assessment, care coordination and rehabilitation is currently only available for hospital in-patients, with no preventative services available to prolong independent community living. Furthermore, sub-acute services for community-dwelling older persons are found to be fragmented; the access to health pathways is unclear, potentially leading to a perverse incentive for hospital admissions to access in-patient geriatric services.

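### The stated 80% power for a 9% difference cannot be reproduced from the printed inputs and is not supported when the 9% is read as a relative change

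*Protocol article*

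**What the plan says.** The Sample size section of the protocol article takes its effect sizes from a cited comparator study covering ED presentations, admissions and bed days: "Pre verses post improvement for these three measures was 10%, 25% and 18% respectively". It then adopts 9% as a cautious effect across ED and in-patient use and adds that "a 10% intra-cluster correlation and between-cluster variations of 30% were assumed for the current study". There are to be at least two GPs per step, "totalling a minimum of 10 GPs (clusters), who will each recruit 10–12 participants to the study". After 25% censoring, the requirement is put at 120 participants, "which will provide 80% power to detect a 9% difference (effect size) in service utilisation" "with statistical significance at the 5% level".

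The Abstract says the trial "uses a stepped wedge cluster design with repeated cross-sectional samples", and Trial design and Sample size use the same label. The Abstract also says: "Data will be collected on each participant at 3-month intervals", with five time points listed. Trial design has patients acting as their own controls, the statistical methods section gives clients a random effect, and Limitations describes paired analyses.

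Limitations also points to the sample size calculation as a reason why a significant effect should be achievable.

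**The concern.** The power statement is a firm figure, and Limitations leans on it. The article does not say whether 9% is a relative change, percentage points or a standardised difference, and it does not define the 30%. Its own context favours the relative scale: a percentage improvement in bed days can only be a relative change, and 9% is cautious beside 10%, 25% and 18% only if it is on the same scale as they are. On that scale the design looks far short of 80%.

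If so, a non-significant primary result would carry little information, while a stated 80% power invites readers to take it as evidence against the model of care. The sizing also follows a sampling scheme that the article contradicts elsewhere, and that choice changes the power materially.

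**Working it through.** **Inputs from the article.** Two-sided 5% level; 10 GPs; ICC ρ = 0.10; 25% censoring. The attrition step reproduces: 120 × 0.75 = 90 evaluable, or m = 9 per GP. The 80% does not, because it needs inputs that are not printed.

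**Assumptions.**
- The 30% is the coefficient of variation of cluster means.
- Every evaluable participant is measured in every period.
- The layouts are standard wedges: 5 steps of 2 GPs with 6 periods; 4 steps (3/3/2/2) with 5; 3 steps (4/3/3) with 4.
- r is the within-person correlation after removing the cluster effect. r = 0 is the cross-sectional model.

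**Implied baseline.**
- Proportion p with an event: (0.3p)² / [p(1 − p)] = 0.10, so p = 0.10/0.19 = 0.526.
- Count with mean μ: 0.09μ / (1 + 0.09μ) = 0.10, so μ = 0.111/0.09 = 1.23 per period.

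**The 9% in SD units.**
- Relative, proportion: 0.09 × 0.526 / √(0.526 × 0.474) = 0.0474/0.499 = 0.095.
- Relative, count: 0.111 / √(1.235 + 0.137) = 0.095.
- Absolute 9 points: 0.09/0.499 = 0.180.

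**Variance of the effect** (linear mixed model, fixed periods, cluster and person random effects, total variance 1):

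Var = 10·s(s + T·t) / (A·s + B·t), with s = (1 − ρ)(1 − r)/m and t = ρ + (1 − ρ)r/m.

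The constants (T, A, B) are (6, 80, 280) for five steps, (5, 61, 184) for four and (4, 45, 111) for three.

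Example, five steps, r = 0: s = 0.10 and t = 0.10, so Var = 10 × 0.10 × 0.70 / (8 + 28) = 0.0194 and SE = 0.139. With r = 0.5: s = 0.05 and t = 0.15, so Var = 0.475/46 = 0.0103 and SE = 0.102.

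Power = Φ(d/SE − 1.96) + Φ(−d/SE − 1.96):

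| Layout | r | SE | 9% relative (d = 0.095) | 9 points absolute (d = 0.180) |
|---|---|---|---|---|
| 5 steps | 0 | 0.139 | 10% | 25% |
| 5 steps | 0.5 | 0.102 | 15% | 43% |
| 5 steps | 0.8 | 0.065 | 31% | 79% |
| 5 steps | 0.9 | 0.046 | 54% | 97% |
| 4 steps | 0 | 0.157 | 9% | 21% |
| 4 steps | 0.5 | 0.114 | 13% | 35% |
| 4 steps | 0.9 | 0.052 | 45% | 93% |
| 3 steps | 0 | 0.179 | 8% | 17% |
| 3 steps | 0.5 | 0.131 | 11% | 28% |
| 3 steps | 0.9 | 0.060 | 35% | 85% |

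**What reaches 80%.**
- Lower baseline, cross-sectional, five steps: a fall from 10% to 1% gives d = 0.09/√(0.055 × 0.945) = 0.395 and power 81%. This is a 90% relative reduction. A t reference with 8 df lowers it to 69%.
- Absolute fall from the 53% baseline, m = 9: r must be about 0.81, 0.85 or 0.88 for five, four or three steps. With five steps and 12 per GP it is about 0.74.
- Relative 9% fall, five steps, m = 9: r must be about 0.95.

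**Role of the ICC.** With five steps, r = 0 and d = 0.18, power is 29%, 26%, 25% and 27% at ICC 0.01, 0.05, 0.10 and 0.20.

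**Recruitment.** With exactly 10 GPs, 10 × 12 = 120 (90 evaluable) and 10 × 10 = 100 (75 evaluable). At 75 (m = 7.5; five steps, r = 0, d = 0.18): s = 0.12, Var = 0.864/37.6 = 0.0230, SE = 0.152, power 22% against 25% at 90.

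**The case against.** A reader might infer that true power is 8% to 43% and that the design fails to deliver 80%. The documents do not support so firm a statement. The baseline, the meaning of the 30%, the number of steps and the within-person correlation are not stated, and the schematic is not shown. The Randomisation section says all clusters receive the intervention for the same length of time, which a standard wedge does not give, so the assumed layouts may not be the trial's. Across admissible readings power runs from about 5% to above 80%. Intermediate cases reach it too: a 20% baseline, 12 per GP, five steps and r = 0.5 give 80%. This objection stands against any single range presented as fact.

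Other tempting readings also fail:
- **The ICC is to blame.** It moves power by only a few points. Effect scale, number measured per GP per period and within-person correlation are what matter.
- **The cross-sectional label explains an inflated 80%.** Ignoring repeat measurement lowers the calculated power (25% against 43% above). The label is wrong, but it errs in the other direction.
- **120 cannot be reached.** Ten is a minimum; 12 GPs with 10 participants each would also give 120.
- **The two sets of results attributed to the same reference conflict.** The Background credits it with "35% fewer Emergency Department (ED) attendances, 52% fewer admissions and 41% fewer days in hospital". Without the source, one cannot tell whether these are different measures, and 9% lies below every figure in both sets.
- **Leaving out a baseline rate is an error.** A condensed article may leave it to the full protocol.

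Nor does any section say that non-significance will be read as no effect; that risk is inferred. What the objection does not answer is that the routes to 80% need inputs the article does not give. The main one, a 90% relative reduction, is hard to call cautious beside improvements of 10–25%.

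**Conclusion.** The point holds in limited form: the 80% cannot be rebuilt from the printed inputs, and the natural relative reading does not support it. With 10 GPs, 9 evaluable each, ICC 0.10, the 30% as a coefficient of variation and 3 to 5 steps, power for a 9% relative fall is about 8–15% at within-person correlation 0–0.5 and 35–54% at 0.9. For an absolute 9-point fall from the implied 53% baseline it is about 17–43% at correlation 0–0.5, and 80% is reached only at about 0.8 or above. These figures depend on the stated assumptions and on a normal approximation.

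Two parts need no assumption. The design is labelled and sized as repeated cross-sections, although the article describes a cohort followed over five time points. And with the minimum of 10 GPs, 120 is met only if every GP recruits 12. The assurance under Limitations is therefore stronger than the calculation can bear.

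**What to change.** - Recompute power for the actual cohort layout (real steps and measurement windows, cluster and within-person correlation), with a stated baseline, a defined 30% and an explicit scale for the 9%.
- Replace the 80%/9% statement with the resulting power or detectable difference, and give it also for 100 recruited (75 evaluable).
- Correct the repeated cross-sectional label in the Abstract, Trial design and Sample size sections.
- Temper the sentence under Limitations, and say that a null primary result will be read from the estimate and its confidence interval.

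The cost is a recalculation and revised wording. No extra patients are needed. The downside is a less favourable stated power.

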#### Participant recruitment

The treating GP, enrolled in the study, will select patients based on set eligibility criteria. The GP will discuss the study with individual patients and invite them to provide verbal consent to be contacted by the project manager to further discuss the project. The project team will arrange a time to meet with interested participants to discuss the OPEN ARCH intervention and study requirements, inviting them to provide informed consent for inclusion in the study. Participants who do not wish to provide consent for inclusion in the OPEN ARCH intervention may still access specialist geriatric assessment via the existing Cairns Hospital Outpatient referral pathway, but they will not be offered access to the OPEN ARCH community care coordination or a geriatric assessment at their GP practices.

Participation in this study is voluntary. Patient participants will be informed that they can withdraw at any time without giving a reason and that refusal to participate will not have any impact on their current or future access to geriatric or GP services. If requested by the participant, any information they may have provided will be withdrawn from the study. It is not anticipated that GPs will withdraw their consent to participate in the study. However, should a GP move their practice or retire, their patient participants will also be withdrawn from the study and they will not be invited to participate in any further data collection. Routine geriatric assessments will still be available to all patients via the usual outpatient referral system and any links with services initiated by enablement officers may continue independently of the OPEN ARCH intervention.

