### Randomisation of general practitioners

All recruited GPs will be randomised as ‘clusters’ at baseline using simple randomisation [17]. Such cluster randomisation allows control for the ‘between GPs variance’. A minimum of two clusters (two GPs) will be commencing the intervention at each step, as per the recommendations of Barker et al. [16], to ensure that the intervention effect estimator maintains the nominal 5% significance level and is reasonably unbiased. All clusters will ultimately receive the intervention for the same length of time.

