#### Inclusion criteria

To be eligible to enter the study, participants must meet the following criteria:A community-dwelling older person with chronic conditions and complex care needs, defined as having multiple morbidities or a social situation that requires the attention of multiple healthcare providers or facilities,○ who is 70 years or older for non-Aboriginal and Torres Strait Islander participants, or 50 years or older for Aboriginal and Torres Strait Islander participants; or○ who is younger than the previous age criteria but has documented chronic or complex age-related conditions (previously only associated with older persons), such as early-onset dementia or arthritis, or another condition.

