### Blinding

As OPEN ARCH requires active involvement, it would not be possible to blind participants or GPs (clusters), nor enablement officers or the project manager [15]. Participants and GPs will be required to make an informed decision for consent, so they will have full disclosure available prior to the consent. Enablement officers providing clinical care will have full knowledge of the participants’ health status throughout the study period. Similarly, the project manager, who will be required to enter the data, will remain un-blinded throughout the study. However, every attempt will be made to blind outcome assessors in order to reduce information or ascertainment bias [21]. Directly asking outcome assessors which intervention they think was administered will judge the success of blinding.

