#### Frequency of analyses

All data will be collected at baseline ‘0’ with retrospective collection for 3 months to time point ‘– 1’, following every 3 months of data collection, at time points ‘1’, ‘2’ and ‘3’ (see Fig. 2), except for participants’ experiences, which will be collected at the end of the study period.

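### Unblinded GPs choose their own patients, and nothing stated keeps the step order from them until enrolment closes, so patient mix may differ by step and bias the effect in either direction

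*Protocol article*

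**What the plan says.** Five parts of the protocol article bear on this.

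- **Randomisation of general practitioners.** The GPs are the clusters and are randomised "at baseline using simple randomisation", with at least two starting at each step. Concealment of the order is not mentioned.
- **Participant recruitment.** "The treating GP, enrolled in the study, will select patients based on set eligibility criteria". The GP introduces the study and asks patients to "invite them to provide verbal consent to be contacted by the project manager to further discuss the project".
- **Inclusion criteria.** Complex care needs are "defined as having multiple morbidities or a social situation that requires the attention of multiple healthcare providers or facilities", and younger patients can enter through an open-ended list of conditions. Under Sample size, each GP recruits only 10–12 people.
- **Blinding.** The article states that "it would not be possible to blind participants or GPs (clusters), nor enablement officers or the project manager". On GPs and participants it adds "so they will have full disclosure available prior to the consent". Blinding is attempted only for outcome assessors.
- **Frequency of analyses.** Data are collected at baseline "with retrospective collection for 3 months to time point" −1, and then every three months. The quarter before baseline is therefore pre-intervention data for every GP.

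Under Statistical methods, the primary analysis is a generalised linear mixed model (GLMM) with fixed effects for time and intervention status and random effects for cluster and client.

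**The concern.** Randomising GPs to steps makes the GPs comparable. It makes their patients comparable only if patients are chosen without knowledge of the start date. Here both people who bring patients in are unblinded, the criteria leave room for judgement, and each list is short. A GP who starts at once might nominate patients in a current crisis, or the frailest on the list. A GP who starts months later has less reason to.

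The planned model gives partial protection. Fixed time effects remove regression to the mean that is common to all steps, and random effects damp stable differences between steps. A temporary excess confined to first-step patients is not removed: it raises their pre-intervention quarter, and its decline coincides with their crossover. The primary outcomes exposed are ED presentations, admissions, bed days and other service use.

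**Working it through.** The article gives no figure on this point, so the check asks how much of a step-dependent difference in patient mix reaches the effect estimate when the true effect is zero.

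**Inputs from the article**
- 10 GPs, at least two per step, ICC 0.10.
- 12 patients per GP, or 12 × 0.75 = 9 after the 25% censoring allowance.
- Data at −3, 0, 3, 6 and 9 months, which gives four three-month windows.

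**Assumptions**
- The step layout, because the design figure is not shown.
- Within-patient correlation ρ from 0 to 0.7 (client share of within-cluster variance).
- A 20% excess in use among first-step patients. Bias scales in proportion to it.
- The same patients are followed throughout, and cell means are analysed on a linear scale.

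**Formula.** The generalised least squares estimate is a weighted sum of GP-by-window means, so bias = excess × (sum of weights on the affected cells). Within a GP, the means share covariance a = ICC + ρ(1 − ICC)/n, and each has extra variance b = (1 − ρ)(1 − ICC)/n.

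**Case that can be checked by hand.** Two steps of five GPs over four windows, starting in windows 2 and 3. The first-step weights reduce to:
- excess in window 1 only (transient): −a/(b + 3a)
- excess in all windows (persistent): b/(b + 3a)

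| n, ρ | a | b | Transient weight | Persistent weight |
|---|---|---|---|---|
| 9, 0 | 0.10 | 0.10 | −0.10/0.40 = −0.25 | 0.10/0.40 = +0.25 |
| 12, 0.7 | 0.1525 | 0.0225 | −0.1525/0.48 = −0.32 | 0.0225/0.48 = +0.05 |

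**Transient excess, other layouts (computed numerically)**
- Four windows, two to four steps at consecutive windows: −0.19 to −0.32. Bias is 20% × 0.19 to 0.32, about 3.7 to 6.4 points towards benefit with unrounded weights.
- Five steps of two GPs, five or six windows: −0.11 to −0.19, or 2.2 to 3.8 points towards benefit.
- Two steps spaced two windows apart: about −0.46, or roughly 9 points. This lies outside the range quoted as the main result, which assumes consecutive steps.

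**Persistent excess**
- All the consecutive-step layouts: +0.02 to +0.25, or 0.4 to 5.0 points *against* benefit.
- At ρ = 0.7: +0.02 to +0.06, or 0.4 to 1.2 points.

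**Half the excess persists** (four windows). The weight is the average of the two cases, for example (−0.25 + 0.25)/2 = 0 and (−0.32 + 0.05)/2 ≈ −0.13. A 20% excess then gives 0 to 2.7 points towards benefit.

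**Effect of dropping the −3 to 0 window.** In the hand case the persistent weight becomes b/(b + 2a). It rises from 0.25 to 0.10/0.30 = 0.33 at ρ = 0, and from 0.047 to 0.0225/0.3275 = 0.069 at n = 12, ρ = 0.7. Across the four-window layouts the rise is roughly 30–90%.

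**The case against.** The strongest objection is that this is silence in a condensed article. The SPIRIT checklist and both figures are not shown, and the order of randomisation, disclosure and enrolment may be set out there or in a fuller protocol. The blinding statement concerns knowing that care is being delivered, and full disclosure concerns information for consent. Neither says that a GP knows the start date when nominating patients. This stands in part. A reader might infer that patients were chosen after the order was known, but the article does not say so. If all were enrolled first, this route to bias closes. What remains is that the article's own sections put selection with unblinded people after a baseline randomisation and state no safeguard.

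A second objection concerns direction. A reader might infer that the bias must favour the intervention. That holds only if the excess is mainly transient. The population has chronic multimorbidity and, under Limitations, is expected to decline, so a purely transient excess is the extreme case. This objection stands.

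A third is that existing features help. Hospital and ED data come from routine records, and the random effects strongly damp a stable mix difference. This is correct, but records do not protect selection and random effects do not remove a transient difference.

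**Conclusion.** The concern holds as a design weakness: followed as written, the plan allows selection that depends on step. It is worth fixing, but the documents do not show that bias occurred.

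Under an assumed, purely transient 20% excess in first-step patients, the shift is about 2 to 6 percentage points towards benefit for steps at consecutive windows. A persistent excess of the same size shifts the estimate the other way, by about 1 point or less when within-patient correlation is high and by up to 5 points when it is zero.

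A reader might set 3.7 to 6.4 points against the 9% design effect and conclude that 41–71% of it could be spurious. The documents do not support that. The 20% is assumed and the layout is unseen. The article does not say whether 9% is absolute or relative, and its promise of equal intervention duration for all clusters does not fit a fixed four-window wedge.

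These figures also assume one cohort followed throughout. The article labels the samples repeated cross-sections but elsewhere has patients as their own controls. If different patients were chosen before and after crossover, any difference between them would pass into the estimate in full.

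**What to change.** **If patients are still to be enrolled.** State that each GP lists and consents all of their patients before the step order is disclosed to the GPs or the project manager. This re-orders two existing activities. The cost is a short delay in telling GPs their start dates.

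**If enrolment is complete.** This is likely, since Trial status puts the study six months past baseline in November 2018.
1. Report the actual sequence of randomisation, disclosure and enrolment.
2. Tabulate baseline characteristics and −3 to 0 month utilisation by step.
3. If the steps differ, add a sensitivity GLMM adjusted for baseline patient characteristics already collected. Such adjustment addresses stable differences better than a transient crisis, so the table by step remains necessary for interpretation.

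A rerun without the −3 to 0 window should be supplementary at most. It discards the first-step GPs' pre-intervention data and increases the pass-through of a persistent mix difference, so it is not a clean test for bias.

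The cost is one table and one extra model, with no additional data collection.
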